# Efficacy of Wearable low-intensity pulsed Ultrasound treatment in the Movement disorder in Parkinson’s disease (the SWUMP trial): protocol for a single-site, double-blind, randomized controlled trial

**DOI:** 10.1186/s13063-024-08092-y

**Published:** 2024-04-22

**Keywords:** Parkinson’s disease, Ultrasonic therapy, Neuromodulation, Low-intensity pulsed ultrasound, Randomized controlled trial

## Abstract

**Background:**

Parkinson’s disease (PD) is a progressive, neurodegenerative illness marked by the loss of dopaminergic neurons, causing motor symptoms. Oral levodopa replacement therapy remains the gold standard in the treatment of PD. It is, nevertheless, a symptomatic treatment. There is currently no effective treatment for PD. Therefore, new therapies for PD are highly desirable. Low-intensity pulsed ultrasound (LIPUS) has been shown to improve behavioral functions in PD animal models. It is a new type of neuromodulation approach that combines noninvasiveness with high spatial precision. The purpose of this study is to establish a new clinical protocol for LIPUS in the treatment of movement disorders in patients with PD.

**Methods:**

This protocol is a single-site, prospective, double-blind, randomized controlled trial (RCT). Forty-eight participants with clinically confirmed PD will be randomly allocated to one of two groups: LIPUS group or sham group. All of the participants continue to use pharmacological therapy as a fundamental treatment. The primary outcome is the difference between groups from baseline to 4 months in the change in the Unified Parkinson’s Disease Rating Scale (UPDRS) motor score (part III). The secondary outcomes include the rating scales such as the Mini-Mental State Examination (MMSE), and other three rating scales, and medical examinations including high-density electroencephalography (hdEEG) and functional magnetic resonance imaging (fMRI). The primary safety outcome will be assessed at 4 months, and adverse events will be recorded.

**Discussion:**

This study represents the clinical investigation into the efficacy of therapeutic LIPUS in the treatment of PD for the first time. If LIPUS is determined to be effective, it could offer a practical and innovative means of expanding the accessibility of ultrasound therapy by using a wearable LIPUS device within a home setting.

**Trial registration:**

Chinese Clinical Trial Registry ChiCTR2100052093. Registered on 17 October 2021.

**Supplementary Information:**

The online version contains supplementary material available at 10.1186/s13063-024-08092-y.

## Introduction

### Background and rationale {6a}

Parkinson’s disease (PD) is a progressive, neurodegenerative disorder marked by the dysfunction and loss of multiple neuronal populations, mainly dopamine neurons located in the substantia nigra, which results in the motor symptoms of PD [1]. Movement-related symptoms include bradykinesia, stiffness of the limbs and torso, resting tremor, and postural instability that may be present at the time of diagnosis and deteriorate over time, even causing physical disability [2–4]. 6.1 million people worldwide were diagnosed with PD in 2016, a figure that was 2.4 times greater than in 1990 [4]. The prevalence of PD rises with age, with 1% of the population over 60 years old suffering from the disease [5], which places a heavy financial burden on families and society.

There are numerous treatments available to help with the motor symptoms of PD, including pharmacologic techniques such as levodopa preparations given with or without other drugs [6, 7], as well as non-pharmacologic techniques that include deep brain stimulation (DBS) and non-invasive therapies such as MRI-guided focused ultrasound (FUS) and low-intensity pulsed ultrasound (LIPUS) [8–10]. DBS is typically considered when patients with a diagnosis of PD experience either the “wearing off” phenomenon or dyskinesias, and these experiences do not respond to medication adjustments [1]. However, DBS has some drawbacks with invasiveness, including stimulation tolerance, infection, hemorrhage, and other risks as therapy with implanted devices [9].

With respect to non-invasive ultrasound therapies, an article reported by Science anticipated that it would show promise in the treatment of brain disorders, offering a safe and predictable method for modifying human brain function [11]. It is a new type of neuromodulation technique that combines noninvasiveness with high spatial precision. As a propagating wave, ultrasound can penetrate biological tissues, including the skull, and its energy can be concentrated into a tiny, restricted area, causing a variety of thermal and non-thermal effects on cells and tissues, depending on several parameters such as frequency, intensity, duty cycle, and exposure period on neurons [12, 13]. Recently, a study demonstrated that FUS subthalamotomy in one hemisphere led to improvements in the motor symptoms of PD, marking a significant milestone [14]. Nevertheless, the utilization of MRI-guided FUS to target the thalamus comes with the potential for enduring complications and side effects, such as finger paresthesia, ataxia, and orofacial paresthesia [15]. In addition, FUS ablation at high temperatures may cause thermal lesion of the neural tissues, possibly resulting in irreversible damage [16].

Compared with FUS ablation, LIPUS can be safely used to regulate neuronal circuits in the central nervous system, inducing therapeutic changes without thermal effect [17, 18]. LIPUS allows for non-invasive penetration through the skull with neuroprotective and reversible neuromodulatory effects, adjustability, and high spatial resolution [19, 20]. Furthermore, pulsed ultrasound is an intermittently delivered ultrasound that minimizes the thermal effects of ultrasound and targets the tissue cells of the lesion without affecting the normal tissue cells [21]. In numerous PD animal models, LIPUS has been shown to stimulate or inhibit neuronal activity and stimulate the motor cortex [22–24]. These findings indicate that LIPUS holds promise as a modality for neuromodulation. Furthermore, to the best of our knowledge, no clinical trial has previously employed LIPUS treatment in patients with PD.

Therefore, the current single-site, prospective, double-blind, randomized controlled trial (RCT) aims to look into the efficacy of LIPUS in the treatment of PD. The trial is the first clinical trial using the self-developed wearable LIPUS device for PD treatment.

### Objectives {7}

The aim of the present study is to evaluate the efficacy of LIPUS as a therapeutic intervention for alleviating motor impairments in individuals with PD. In order to achieve the aim of this study, the subsequent research inquiries have been formulated:Is the ultrasound stimulation administered in the LIPUS group more effective than the sham group without ultrasound stimulation in treating movement disorders in PD patients?What cerebral modifications do patients experience as a result of LIPUS therapy?Apart from motor symptoms, are there changes in other symptoms, like depression and anxiety, that may occur?

### Trial design {8}

The trial is a prospective, double-blind, single-site control clinical superiority trial that will enroll patients diagnosed with PD based on the U.K. Brain Bank Clinical Criteria from Shanghai Jiao Tong University of Medicine Affiliated Sixth People's Hospital [25]. Participants will be randomly assigned to two groups in a 1:1 allocation ratio: the LIPUS group (600 kHz, 1.0 W/cm^2^) and the sham group. This manuscript follows the Standard Protocol Items: Recommendations for Interventional Trials (SPIRIT) guideline [26]. The flow chart depicting the study protocol is presented in Fig. 1.

**Fig. 1 Fig1:**
[figure not shown]
Participant flow chart

## Methods: participants, interventions, and outcomes

### Study setting {9}

This is a single-center, prospective, double-blind, randomized controlled trial that will be conducted at the Shanghai Jiao Tong University of Medicine Affiliated Sixth People’s Hospital.

### Eligibility criteria {10}

Inclusion criteria are as follows: (1) subjects with a diagnosis of PD based on UK Brain Bank Criteria as confirmed by a neurologist; (2) Hoehn and Yahr stage in the on-medication state of 2.5 or less; (3) in principle, the pharmacological regimen remains unchanged during LIPUS treatment; (4) men and women, ranging in age from 18 to 80 years old; (5) available to participate in follow-up for the duration of study and give consent; (6) subjects are examined by transcranial sonography, having a sufficient temporal bone window and substantia nigra echogenicity (contralateral and ipsilateral) so that they can be targeted by a wearable LIPUS device.

Exclusion criteria are as follows: (1) Hoehn and Yahr stage of 2.5 or higher; (2) presence of another central neurodegenerative disease. These include Parkinsonism-Plus syndrome, dementia with Lewy bodies, Alzheimer’s disease, and amyotrophic lateral sclerosis; (3) previous history of intracranial hemorrhage or severe head injury; (4) a history of ischemic stroke or a stroke within the previous 6 months; (5) subjects with malignant brain tumors or a history of seizures within the past year; (6) pregnancy or lactation; (7) Parkinsonian symptoms, which are a side effect of any medication; (8) subjects who have previously undergone deep brain stimulation or nerve nucleus ablation; (9) subjects exhibiting any ethanol or substance abuse behaviors; (10) current medical condition that is causing abnormal bleeding and/or coagulopathy; (11) subjects who are unable to communicate with the researchers or participate in other clinical studies in the meantime.

### Who will take informed consent? {26a}

The research assistant ([name]) will obtain informed consent from participants before conducting the baseline evaluation in the participant reception room. Participants will engage in a 30-min group discussion with a research assistant. This session will encompass an overview of the PD therapy protocol for the trial and detailed instructions on how to use the wearable LIPUS device. Participants will receive an explanation of the study’s purpose, their role in it, and the potential benefits and risks involved. Meanwhile, participants will also be provided with an instructional video, produced by the research team, demonstrating the correct usage of the LIPUS device. If participants have any questions, they are encouraged to ask, and they have the freedom to decide whether to participate in the study after fully comprehending the information provided.

### Additional consent provisions for collection and use of participant data and biological specimens {26b}

No additional biological samples were collected during the study, and no subject data are currently available for future research endeavors. If any participant data relevant to subsequent studies are required, additional consent will be obtained from the participants.

### Interventions

#### Explanation for the choice of comparators {6b}

To evaluate the efficacy of LIPUS therapy, we chose the use of null stimulation as the comparator. It is important to note that each LIPUS wearable device is equipped with mechanical vibration, whether or not ultrasonic waves are employed. The subjects are unable to distinguish the presence or absence of ultrasonic stimulation.

### Intervention description {11a}

Participants will self-administer LIPUS treatment at home for 4 months using a self-developed wearable LIPUS device based on dopaminergic medication, the quantity of which will not be adjusted during the trial until the condition worsens or adverse effects occur. The LIPUS group received pulsed therapeutic ultrasound (Shanghai, China) through the temporal bone window with a frequency of 600 kHz, an intensity of 1.0 W/cm^2^, a duty cycle of 50% (10 ms on, 10 ms off), and a duration of 30 min. This LIPUS treatment will be conducted once a day for a total duration of 4 months.

Each participant will be initially guided by ultrasound through the skull to the bilateral substantia nigra and striatum by a senior radiologist [27]. Then, the radiologist will mark the stimulation site with a marker, and a research assistant will capture a photograph to document the precise targeted site for each participant. Typically, the targeted site is usually at the tip of the ear [27, 28]. The treatment site of the LIPUS device will be positioned on these two marked target sites.

Participants in the sham group, who will only receive the basic medication, will also be provided with ultrasound devices that do not have any therapeutic effect without LIPUS stimulation. The trial team’s other procedures and activities will be consistent and identical for both groups.

### Criteria for discontinuing or modifying allocated interventions {11b}

In this study, the criteria for discontinuing the intervention will be (1) participants who are unable to complete the clinical study, (2) participants who voluntarily withdrew informed consent, and (3) participants who experience serious adverse events. As of now, no adverse events have been reported during the course of LIPUS treatment.

### Strategies to improve adherence to interventions {11c}

To enhance compliance with the interventions, we offer trial-related assessments of the rating scales and medical examinations, which encompass ultrasound examinations, high-density electroencephalography (hdEEG), and functional magnetic resonance imaging (fMRI) from the baseline to the 4-month treatment period at no cost to the participants.

### Relevant concomitant care permitted or prohibited during the trial {11d}

All participants will be provided with a pharmacological regimen as part of the trial. It is strongly discouraged for participants to seek additional treatments beyond what is assigned in the protocol during the intervention period. Participants are obligated to report any deviations from the protocol, which includes adjusting medications for PD or adding other treatments.

### Provisions for post-trial care {30}

Trial interventions are designed to inflict minimal to no harm. If a participant suffers any injury due to participating in the trial, we will evaluate, document, provide appropriate medical care, and pay for all related medical expenses.

### Outcomes {12}

#### Primary outcome

The primary effectiveness outcome will be the difference in mean change (at baseline, 2 months, and 4 months) across groups (LIPUS vs sham treatment) according to blinded site evaluation of the UPDRS III score for the affected side. The primary outcome is calculated as the sum of the unilateral items for the following: speech, facies, tremor in resting, intentional tremor, rigidity, rapid movements of the fingers, rapid hand movements, alternating movements, leg movements, getting up from a chair, posture, posture stability, starting walking, and bradykinesia in the third section (motor). The scoring system includes the following: 0 points = no involvement; 1 = detectable disorders; 2 = moderate disorders; 3 = considerable disorders; 4 = no function or severe disorders [29]. Therefore, the primary endpoint score ranges from 0 to 56, with higher scores suggesting worse parkinsonism.

Meanwhile, Fahn and Elton created the Unified Parkinson’s Disease Rating Scale (UPDRS), which is made up of six elements. These are as follows: (I) the state of intellectual and mood disorders; (II) activities of daily living (separately for phase “on” and “off”); (III) motor examination; (IV) complications of treatment; (V) stages of the disease; (VI) self-assessment of independence using the Schwab and England Scale. Furthermore, the subjective, patient-derived Activities of Daily Living (Part II) component of the UPDRS corresponds well with the objective, physician-derived motor section (Part III) [30].

### Secondary outcomes

The following secondary outcomes of this trial will be measured during the 4-month follow-up visit as listed and explained below:

The MMSE (Mini-Mental State Exam) for assessment of cognitive function (includes tests of orientation, attention, memory, language, and visual-spatial skills; range 0–30 with a higher score suggesting better cognitive function) at baseline, 2 months, and 4 months [31].

The BDI (Beck Depression Inventory) for measurement of the severity of depression (range 0–63 with a higher score indicating more severe depressive symptoms) at baseline, 2 months, and 4 months [32].

The BAI (Beck Anxiety Inventory) for measurement of anxiety (range 0–63 with a higher score indicating more severe anxiety symptoms) at baseline, 2 months, and 4 months [33].

High-density electroencephalography (hdEEG) for the assessment of cognitive function changes at baseline, 2 months, and 4 months [34].

Functional magnetic resonance imaging (fMRI) to investigate brain changes associated with the motor and non-motor symptoms at baseline and 4 months [35].

### Participant timeline {13}

The participant timeline is shown in Table 1.

**Table 1 Tab1:** Study evaluation procedures and timeline

Study procedure	Medical evaluation	Enrolment visit	2 months	4 months
Determine eligibility	√	√		
Obtain signed consent		√		
Other medical and demographic data		√		
Give instructions for LIPUS devices		√		
Outcome measures				
Unified Parkinson’s Disease Rating Scale		√	√	√
Other rating scales		√	√	√
High-density electroencephalography		√	√	√
Functional magnetic resonance imaging		√		√

#### Sample size and power {14}

The sample size and power calculations were centered on the primary outcomes, which pertained to the alterations in UPDRS III scores from the baseline assessment to the 4-month follow-up assessment after 4 months of LIPUS treatment. In accordance with the findings derived from the limited sample study involving 20 patients, the LIPUS group exhibited a mean change of 5.54 ± 8.03, while the sham group showed a mean change of − 0.71 ± 2.25. The researcher utilized the sample size calculation software PASS to compute the sample size for each group, which was *n*_1_ = *n*_2_ = 21 (1:1 allocation ratio), to detect differences with a two-sided significance level of 0.05 and 90% power calculations. With the consideration of a 10% dropout rate, the final sample size is expected to be 48. In the prior investigation [36], wherein a clinically meaningful alteration in UPDRS III scores was established as a 5-point disparity, the study determined that the efficiency of the existing sample size in power calculations reached 0.8078.

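### The stated power of 0.8078 for a 5-point UPDRS III difference holds only if all 48 participants supply 4-month data; with the plan's own 10% dropout it is about 0.76

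*Protocol article*

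**What the plan says.** All the figures are in the protocol article, Sample size and power {14}. From a study of 20 patients, "the LIPUS group exhibited a mean change of 5.54 ± 8.03" and "the sham group showed a mean change of − 0.71 ± 2.25". The number per group is given as "21 (1:1 allocation ratio"), chosen "to detect differences with a two-sided significance level of 0.05 and 90% power calculations". The total is then raised for attrition: "With the consideration of a 10% dropout rate, the final sample size is expected to be 48". The last sentence cites a prior investigation in which "a clinically meaningful alteration in UPDRS III scores was established as a 5-point disparity" and reports that "the study determined that the efficiency of the existing sample size in power calculations reached 0.8078". It does not say whether that power refers to the 48 enrolled or to the smaller number expected to be evaluable.

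Three other sections bear on what happens to dropouts:

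- Plans to promote participant retention and complete follow-up {18b} says that data from participants who stop during the treatment phase are not kept for analysis.
- Statistical methods for primary and secondary outcomes {20a} says that the primary outcome is analysed by intention to treat in everyone randomised, with multiple imputation.
- The section on non-adherence and missing data {20c} expects few missing values and names last observation carried forward.

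**The concern.** The paragraph holds two power figures on two different bases. The 90% figure is computed on 21 evaluable participants per arm, and the step to 24 per arm exists only to absorb dropout. If the 0.8078 is computed on 24 per arm, the same extra participants are used twice: once as an allowance for loss, and once as people who supply a 4-month score.

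This matters because 5 points is the difference the article itself puts forward as clinically meaningful, while the 6.25 points behind the 90% figure is an estimate from a 20-patient study. A reader weighing a null result will look to the 5-point figure. Whether it lies just above or clearly below 80% affects how much reassurance that reader takes from it.

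**Working it through.** **Inputs** (all from Sample size and power {14}): SDs of change 8.03 (LIPUS) and 2.25 (sham); difference in the 20-patient study 5.54 − (−0.71) = 6.25; clinically meaningful difference 5; two-sided alpha 0.05; 21 per arm; 10% dropout; total 48. The article does not name the test. I tried three and kept the one that reproduces its figures.

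**Method.** Two-sided unequal-variance (Welch) t test with n per arm:

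- SE = √[(8.03² + 2.25²)/n] = √(69.5434/n)
- df = (n − 1) × (8.03² + 2.25²)² / (8.03⁴ + 2.25⁴) = 1.1561 × (n − 1)
- power = probability that a noncentral t with this df and noncentrality (difference/SE) falls outside ± the 97.5% point of t

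**Step 1: the main calculation.** Difference 6.25.

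- n = 20: SE 1.865, noncentrality 3.352, df 22.0, power 0.893
- n = 21: SE 1.820, noncentrality 3.435, df 23.1, power 0.908

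So 21 is the smallest number per arm that reaches 90%, as stated.

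**Step 2: the dropout inflation.** 21/0.9 = 23.3, rounded up to 24 per arm; 2 × 24 = 48, as stated.

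**Step 3: the 5-point power.** Same test, difference 5.

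| Evaluable per arm | SE | Noncentrality | Power |
|---|---|---|---|
| 24 (no dropout) | 1.702 | 2.937 | 0.8078 |
| 23 | 1.739 | 2.876 | 0.790 |
| 22 | 1.778 | 2.812 | 0.770 |
| 21.6 (10% dropout: 48 × 0.9 / 2) | 1.794 | 2.787 | 0.762 |
| 21 (main calculation) | 1.820 | 2.748 | 0.749 |

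The stated value is matched to four decimals at 24 per arm and at no other row. A simulation with 200,000 replicates agrees: 0.807 at 24 per arm and 0.750 at 21.

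**Step 4: could another test give 0.8078 at 21 per arm?** No. With 21 per arm the equal-variance t test gives 0.765 and the normal approximation 0.785. With 24 per arm they give 0.820 and 0.836.

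**Step 5: difference detectable with 80% power** (Welch): 4.95 points at 24 per arm, 5.24 at 21.6 and 5.32 at 21.

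**Step 6: size of the gap.** 0.8078 − 0.762 = 0.046 with 10% dropout; 0.8078 − 0.749 = 0.059 with 21 per arm. The second case is a loss of 6 of 48, or 12.5%, because rounding 23.3 up to 24 leaves slightly more than 21 after a 10% loss.

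**The case against.** **The figure is not miscalculated.** The sentence giving the total of 48 comes just before the power statement, so the sample size meant there can be read as 48, and for 48 evaluable participants 0.8078 is right. This stands. A reader might infer an arithmetic error; the recomputation does not support that. The defect is an unlabelled basis that differs from the basis of the 90% figure.

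**All 48 may be analysed.** Section {20a} promises intention to treat with multiple imputation and {20c} expects little missing data, so the analysed number could be 24 per arm. This stands in part. If nobody is lost, 0.8078 applies. It does not rescue the figure under the plan's own 10% dropout, for three reasons. Section {18b} discards the data of those who stop early, in conflict with {20a}. The inflation step itself treats dropouts as lost information. Imputing a 4-month score from earlier visits recovers at most part of what an observed score would give. How much the 2-month visit would recover cannot be worked out from the article, so 0.76 is the value if dropouts contribute nothing.

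**The sentence is supplementary.** It set neither the 21 nor the 48, and {20a} commits to 95% confidence intervals, which show directly whether 5 points is excluded. This stands and limits the severity.

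**The sham SD.** A reader might go further and say that power is much lower still, because 2.25 comes from a very small study. At 21 per arm, sham SDs of 4, 6 and 8.03 would give 0.69, 0.61 and 0.50. Taking those as SDs for the sham arm is an assumption; the article gives only 2.25 for it. They say nothing about dropout and are not part of this point.

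**Conclusion.** The point holds as a matter of labelling and consistency. The 0.8078 is the power for 5 points with no dropout. With the plan's own 10% dropout it is about 0.76, and with the 21 per arm used for the main calculation about 0.75, so the type II error at 5 points is about 24% to 25% rather than 19%. The article's claim stays above 80% only by counting the dropout allowance as observed data.

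This rests on the article's SDs of 8.03 and 2.25, on the Welch test (inferred from its exact match to both the 21 and the 0.8078), and on dropouts adding no information to the 4-month comparison.

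A reader might infer that the trial is undersized or that enrolment should rise. The document does not support that: the trial was sized for 6.25 points at 90% power, and that holds at 21 per arm (0.908). Severity is low to moderate.

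**What to change.** Replace the last sentence of Sample size and power {14} with wording such as:

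> Power for a 5-point difference (SDs 8.03 and 2.25, unequal-variance t test, two-sided 0.05) is 0.81 if all 48 participants are evaluable, about 0.76 with 10% dropout, and about 0.75 with 21 evaluable per arm; the difference detectable with 80% power is about 5.2 points with 10% dropout and 5.3 points with 21 per arm.

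A sham-SD sensitivity range may be added, but it is optional and must be labelled as an assumption.

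The cost is one sentence and a slightly less favourable figure. Enrolment, visits and analysis do not change. Recruitment was scheduled to end in November 2023 (Trial status), so the practical places for the correction are the protocol record and the results report.
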